### Discontinuation criteria

Participants will be discontinued from the trial if a high level of medical or psychiatric risk is indicated. This includes severe mood instability requiring inpatient hospital admission (e.g., acute suicidality or deliberate self-harm), severe medical complications as confirmed by GP, or if the participant’s BMI drops below 19. Participants will also be discontinued if they are considered to have disengaged from the intervention evidenced by three weeks of non-completion of the online BEeT session or three consecutive missed telemedicine sessions (only for clinician-supported BEeT group).

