### Adherence strategies

The BEeT platform contains in-built reminders to prompt engagement with the intervention. These include email notifications to alert participants to when a new online BEeT session is available and an automatic text message at approximately 6 p.m. to participants who have not made a food monitoring entry in the previous 24-h period. In addition, participants will be able to create their own personalised reminders specific to their weekly goals.

Additional efforts to re-engage participants in the pure self-help BEeT or WLC groups will consist of written contact via email to the participant after one week of disengagement, a phone call from researchers or clinicians after two weeks consecutive weeks of disengagement, and a letter to the participant and GP after three consecutive weeks of disengagement. The participant will be given an additional two weeks to reengage before they are discontinued from the trial.

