#### Compliance

Measures of compliance will be monitored via the online platform on which the BEeT intervention is hosted. These include the number of self-monitoring entries logged per day, the amount of time taken to complete each online BEeT session, and the time between completion of each BEeT session. The compliance data will be included in statistical analyses of intervention response to determine their effects on key clinical and health economic outcomes.

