### Statistical methods

Initial exploratory analysis will be conducted to ensure baseline comparability between the two intervention groups and across sites. An intention to treat analysis will be conducted. Multiple imputation analysis will be implemented in accordance with missingness assumptions that fit the data (missing at random vs missing not at random), followed by a sensitivity analysis where appropriate. Generalised linear mixed modelling (GLMM) will be used to compare the effectiveness of pure self-help BEeT versus clinician-supported BEeT vs. WLC, collapsed across settings, using change in objective binge episode frequency as the primary outcome. Co-variates in the model will include baseline information of participant age, illness severity and length of illness. This will allow for assessment of the impact of participant characteristics on the key outcomes. Changes in secondary outcomes, such as psychological distress and quality of life, will also be analysed using a GLMM framework.

Time-to-event statistical methods, in particular survival analysis (cox proportional hazard modelling), will be used to examine non-compliance measures (e.g., time spent using intervention, dropout rates) and the factors impacting it (e.g., symptom severity, comorbid mental health difficulties). GLMM analysis will be used to consider the clinician-supported BEeT subgroup and factors impacting change in the EDE-Q, such as treatment setting and clinician experience to determine if the main outcome is affected by the setting in which treatment is delivered. Descriptive analysis will investigate the embeddedness and implementation of the treatment based on the clinician and the patient questionnaires.

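### The discontinuation rules conflict (three weeks or five), so dropout taken from discontinuation records could differ between arms when true disengagement does not

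*Protocol article*

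**What the plan says.** Three parts of the protocol article bear on this.

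- **Discontinuation criteria.** A participant counts as disengaged, and is discontinued, after "three weeks of non-completion of the online BEeT session or three consecutive missed telemedicine sessions (only for clinician-supported BEeT group". The online-session trigger carries no restriction by arm. The telemedicine trigger can apply only in the supported arm.
- **Adherence strategies.** A stepped contact procedure is set out for two groups only: "Additional efforts to re-engage participants in the pure self-help BEeT or WLC groups will consist of written contact via email" after one week, then a telephone call after two, then a letter after three. It ends: "The participant will be given an additional two weeks to reengage before they are discontinued from the trial". No equivalent is given for the supported arm.
- **Statistical methods.** Survival methods, Cox modelling in particular, "will be used to examine non-compliance measures (e.g., time spent using intervention, dropout rates) and the factors impacting it". The explanatory variables are described as "the factors impacting it (e.g., symptom severity, comorbid mental health difficulties".

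The Compliance section adds that the platform records, among other things, "the time between completion of each BEeT session".

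**The concern.** For pure self-help the two procedural sections cannot both hold: the same lapse leads to discontinuation at three weeks under one and at five under the other. If the five-week version is applied, it covers self-help and waitlist but not the supported arm. A discontinuation record then reflects the arm's procedure as well as the participant's behaviour. The supported arm also has a second trigger that the others lack.

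The Introduction presents clinician support as a possible answer to high non-adherence in digital treatment, so readers will look for dropout by arm. An artefact here would work against the supported arm: it could mask a real benefit or suggest a harm.

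A smaller point concerns the phrase time spent using the intervention. It can mean time until use stops, or amount of use. Only the first is a survival time.

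**Working it through.** The article gives no event count, hazard ratio or power for the Cox analysis, so there is no stated figure to reproduce.

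**Step 1: the rules side by side**

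| Arm | Discontinuation criteria | Adherence strategies |
|---|---|---|
| Clinician-supported | 3 weeks without an online session, or 3 missed telemedicine sessions | not covered |
| Pure self-help | 3 weeks | 3 + 2 = 5 weeks |
| Waitlist | 3 weeks as worded, but no BEeT access while waiting | 3 + 2 = 5 weeks |

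**Step 2: consequence if the five-week reading governs and dropout is dated at discontinuation**

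Inputs from the article: lags of 3 and 5 weeks, a 12-week post-intervention assessment, 55 participants per arm and planning dropout of 16%. Assumptions: a constant weekly hazard h of stopping, equal in both BEeT arms, and a window that closes at week 12. To be recorded by week 12, a lapse must begin by week 12 − 3 = 9 in the supported arm and by week 12 − 5 = 7 in self-help. Recorded dropout is therefore 1 − exp(−9h) against 1 − exp(−7h).

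If the planning dropout of 16% is spread over the 10-week programme, h = −ln(0.84)/10 = 0.0174. The values 0.03 and 0.05 are assumed; they imply 1 − exp(−0.3) = 26% and 1 − exp(−0.5) = 39% stopping by week 10.

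| Weekly hazard | Supported | Self-help |
|---|---|---|
| 0.0174 | 1 − exp(−0.157) = 14.5% | 1 − exp(−0.122) = 11.5% |
| 0.03 | 1 − exp(−0.27) = 23.7% | 1 − exp(−0.21) = 18.9% |
| 0.05 | 1 − exp(−0.45) = 36.2% | 1 − exp(−0.35) = 29.5% |

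**Step 3: apparent hazard ratio and error rate**

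The ratio of cumulative hazards at week 12 is 9h/7h = 1.29 at any h. Cox models fitted to simulated trials with 55 per arm and no true difference agree:

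- At 1.7% per week, the hazard ratio is about 1.30 and the error rate at 0.05 is 0.052.
- At 3% to 5% per week, the hazard ratio is about 1.33 and the error rate is 0.09 to 0.13.

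A true hazard ratio of 0.70 would be seen as about 0.70 × 1.33 = 0.93.

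**Step 4: sensitivity to the window**

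If the window closes at week 10, the cumulative-hazard ratio is 7h/5h = 1.4. Simulation, with 16% to 47.2% truly stopping by week 10 (the upper figure is the highest dropout cited in the Introduction), gives hazard ratios of about 1.5 to 1.6.

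**Step 5: does a common definition remove it?**

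With a three-week lag in both arms, the simulated hazard ratio is about 0.98 and 4.5% to 5.2% of tests reject. Dating at last engagement returns 1.00 when there is no true difference and 0.70 when the true ratio is 0.70.

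**The case against.** The strongest objection is that the bias needs three conditions, none of which the article fixes: the five-week reading governs, dropout is dated at discontinuation, and arms are compared. A reader might infer that the planned Cox analysis relies on discontinuation dates and is therefore biased. The text does not support that. It gives no event, time origin or censoring rule, and an article may leave these to an analysis plan. The Compliance section points to platform logs, which could supply an unbiased date. Arm is not among the named factors, although those are only examples. This stands, and it makes the bias conditional.

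A reader might also take three weeks in one arm and five in the others as the settled design. It is not, because the Discontinuation criteria section applies the three-week session rule to everyone. One could instead read the Adherence strategies section as spelling out how that rule is carried out. That removes the contradiction for self-help, but it leaves exactly the arm-dependent lag examined above.

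Nor is time spent using the intervention necessarily unsuited to Cox modelling: time from start until use stops is an ordinary duration. The phrase is ambiguous, not wrong.

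On size, the inflated error rate appears only at hazards above the one implied by the article's own 16%. At that figure the test is close to nominal, though the estimate is still shifted to about 1.30. On importance, a between-arm adherence comparison is not among the listed aims, so this is a secondary analysis.

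The Discussion does say that re-engagement contacts will be counted so that the analysis can account for them. That addresses the effect of contact, not the unequal lag.

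**Conclusion.** The point holds as an internal conflict with a conditional statistical consequence. The two procedural sections disagree for pure self-help and must be reconciled. If dropout is then taken from discontinuation records under the five-week reading, any comparison or report of dropout by arm carries an artefact against the supported arm: about 3 percentage points at the article's planning dropout (14.5% − 11.5%) and about 7 at a 5% weekly hazard (36.2% − 29.5%), with a hazard ratio of about 1.3.

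These figures assume a constant and equal hazard, a 12-week window, no return during the extra two weeks, and no effect of the telemedicine trigger. The article does not show that the planned analysis will be done this way. The primary outcome analysis is outside this point.

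**What to change.** 1. Reconcile the Discontinuation criteria and Adherence strategies sections, and state which arms each provision covers. Which rule applies is for the investigators.
2. For the analysis, define disengagement identically in both BEeT arms from the platform log, independently of the discontinuation procedure. The event is programme not completed and no session completed for a common, pre-set gap, dated at the last completed session. Completers and those still active are censored. The gap is needed because everyone has a last session and each session opens only after the previous one is finished, so without it slow but active users would count as dropouts. The gap should not exceed the shortest inactivity after which anyone is discontinued; otherwise the procedure re-enters the definition. Leave out the waitlist period, when there is no BEeT use.
3. State whether time spent using the intervention means time until use stops (Cox is suitable) or amount of use (use a regression suited to that type of outcome).

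The cost is wording in the protocol and analysis plan. The Compliance section already provides for the session timing data, so no new data collection is needed.

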## Discussion

This trial is the first to examine the effectiveness, feasibility, and cost-effectiveness of a CBT-based, online self-help program in an Australian cohort of BN patients in real world healthcare settings. Should the results demonstrate the BEeT program to be an effective intervention, this research has the potential to change the treatment landscape for individuals with BN. Low-intensity programs, such as BEeT, are designed to be integrated within the early stages of a stepped-care model, either as a pure self-help intervention or a clinician-supported intervention [23, 73]. By doing so, there can be improved resourcing in busy clinical services, more BN patients can receive treatment sooner, and hopefully result in a shorter duration of the illness and reduced burden to the individual and healthcare system.

There are several strengths of this trial. Firstly, the three-arm randomised controlled study design allows for assessment of the added benefits of clinician support in comparison to independent engagement with BEeT. Importantly, such outcomes must be considered when defining resource requirements for successful delivery of the intervention, for example the intensity of therapeutic support and necessary level of training of non-specialist clinicians. Secondly, the multisite design provides scope for implementation research through examination of the real-life application of a stepped care approach to EDs within the Australian healthcare system. Data will be collected from the perspective of participants, clinicians, and site managers to determine the site-specific variables affecting implementation of a supported self-help program across multiple outpatient clinics. Implementation science is a rapidly growing field of research, which is vital in facilitating the transfer of evidence-based interventions into clinical practice and community settings [74]. This is particularly important to consider within the domain of digital interventions, with research suggesting poor association between research studies on web-based interventions and meaningful outcomes for patients in clinical settings [75]. Thirdly, our trial includes an online training package for clinicians delivering the intervention, allowing for assessment of its capacity to upskill clinicians to guide patients through a self-help program without previous training in ED treatment.

There are limitations of this trial. To begin, the fidelity of the pure self-help intervention group may be compromised by the degree of contact between the researcher and participant as part of the disengagement protocol. This represents a potential confounding factor as such contact may limit the truly independent nature of the pure self-help condition. For example, follow up phone calls and emails made by researchers may create accountability for the participant to complete the sessions. To account for this in the statistical analyses, the frequency of contact initiated as part of the disengagement protocols will be recorded by research staff. Additionally, this trial started as the COVID-19 outbreak began globally in early to mid-2020. Due to the multisite design of the trial, the COVID-19 pandemic imposed operational challenges and significantly delayed recruitment. Equally, there were advantages of the digital delivery of this intervention in allowing for by-distance mental healthcare within a COVID-safe framework. Also, the mandatory GP medical screening of participants may form a barrier to participation for some individuals and could potentially impinge upon the key advantages of digital treatments, that being it’s accessibility and anonymity. Finally, a high risk of bias may be present due to non-blinding of trial participants [76].

To conclude, this study attempts to address the need for innovative evidence-based digital interventions through the evaluation of a recently developed modern, online platform designed by an interdisciplinary team of digital programmers and designers as well as clinical staff [77]. It is hoped that this study contributes further to current knowledge regarding the ways in which we can effectively adopt an evidence-based mental health strategy which leverages innovative technology.

## Data Availability

Not applicable.

## Abbreviations

BN: Bulimia nervosa
ED: Eating disorder
CBT: Cognitive behavioural therapy
BEeT: Binge eating etherapy
WLC: Waitlist control
BMI: Body mass index
GLMM: Generalised linear mixed modelling
QALYs: Quality adjusted life years
ICERs: Incremental cost-effectiveness ratios
